# A multi-center, randomized, 12-month, parallel-group, feasibility study to assess the acceptability and preliminary impact of family navigation plus usual care versus usual care on attrition in managing pediatric obesity: a study protocol

**DOI:** 10.1186/s40814-023-01246-w

**Published:** 2023-01-23

**Keywords:** Attrition, Canada, Chronic Disease Management, Feasibility study, Obesity, Pediatric, Randomized trial

## Abstract

**Background:**

Pediatric obesity management can be successful, but some families discontinue care prematurely (i.e., attrition), limiting treatment impact. Attrition is often a consequence of barriers and constraints that limit families’ access to obesity management. Family Navigation (FN) can improve access, satisfaction with care, and treatment outcomes in diverse areas of healthcare. To help our team prepare for a future effectiveness trial, the objectives of our randomized feasibility study are to (i) explore children’s and caregivers’ acceptability of FN and (ii) examine attrition, measures of study rigor and conduct, and responses to FN + Usual Care vs Usual Care by collecting clinical, health services, and health economic data.

**Methods:**

In our 2.5-year study, 108 6–17-year-olds with obesity and their caregivers will be randomized (1:1) to FN + Usual Care or Usual Care after they enroll in obesity management clinics in Calgary and Mississauga, Canada. Our Stakeholder Steering Committee and research team will use Experience-Based Co-Design to design and refine our FN intervention to reduce families’ barriers to care, maximizing the intervention dose families receive. FN will be delivered by a navigator at each site who will use logistical and relational strategies to enhance access to care, supplementing obesity management. Usual Care will be offered similarly at both clinics, adhering to expert guidelines. At enrollment, families will complete a multidisciplinary assessment, then meet regularly with a multidisciplinary team of clinicians for obesity management. Over 12 months, both FN and Usual Care will be delivered virtually and/or in-person, pandemic permitting. Data will be collected at 0, 3, 6, and 12 months post-baseline. We will explore child and caregiver perceptions of FN acceptability as well as evaluate attrition, recruitment, enrolment, randomization, and protocol integrity against pre-set success thresholds. Data on clinical, health services, and health economic outcomes will be collected using established protocols. Qualitative data analysis will apply thematic analysis; quantitative data analysis will be descriptive.

**Discussion:**

Our trial will assess the feasibility of FN to address attrition in managing pediatric obesity. Study data will inform a future effectiveness trial, which will be designed to test whether FN reduces attrition.

**Trial registration:**

This trial was registered prospectively at ClinicalTrials.gov (#NCT05403658; first posted: June 3, 2022).

**Supplementary Information:**

The online version contains supplementary material available at 10.1186/s40814-023-01246-w.

## Background

Pediatric obesity is prevalent [1], persistent [2, 3], and complex [4, 5]. Without intervention, obesity and its consequences usually track into adulthood [6–8], a pattern that entrenches with increasing obesity severity [9] and underscores the value of accessible and effective interventions. However, successful obesity management (i.e., reducing or stabilizing weight gain; improving obesity-related consequences) is challenging. Multidisciplinary interventions centered on family lifestyle and behavior changes can help children to manage their obesity [10, 11]. Success in managing obesity is typically achieved by adhering to treatment regimens and regularly attending clinical appointments [12]. Effective lifestyle and behavioral interventions require a moderate to high intervention dose (i.e., > 25 h of clinic contact over 6–12 months [13]) to optimize health benefits [14, 15]. Achieving this dose is difficult for many families due to barriers and constraints to accessing care, such as schedule availability, transportation costs, and variable motivation [16, 17]. Even the best obesity management interventions are undermined when families discontinue care prematurely [18].

In managing pediatric obesity, we aim to minimize attrition (i.e., permanently discontinue care [19]) so children and families benefit from care. Attrition levels are as high as 80% [20]; 30–40% attrition is common [21–24]. Attrition wastes healthcare resources, discourages families from accessing services in the future [25, 26], and exacerbates health inequities for families with limited resources [27]. High attrition in pediatric obesity management was first reported as a problem > 50 years ago [28], but experimental research is lacking given the magnitude of the problem, highlighting the need to create and test interventions to improve access, reduce attrition, and manage obesity successfully [29].

Despite the lack of experimental research, descriptive research has produced some insights about attrition. For example, a review [16] published by our team members revealed higher attrition in children ≥ 12 years old and among families receiving social assistance. Reasons for attrition included logistical barriers and unmet family needs or expectations. Often, attrition involves multiple factors [21, 26, 30], with a series of missed or cancelled appointments preceding attrition, reducing the potential for positive treatment outcomes. Conversely, families continue attending appointments for several reasons, including anticipated and actual treatment benefits and high-quality care [31]. Ongoing attendance can be facilitated by flexible family schedules, choice of clinic appointment times, adequate family resources, and high motivation in children [31]. Some families can reduce barriers and eliminate constraints that limit access to obesity management, but many lack social support and financial resources, so could benefit greatly from enhanced care.

Several strategies have the potential to reduce attrition. Along with using multiple modes of communication with patents and families [32], clinical researchers recommend combining strategies to enhance clinic appointment attendance [33], including reducing wait times, making reminder calls [34], and applying techniques such as motivational interviewing to reduce missed or cancelled appointments [35]. Missed appointments are lost opportunities, so clinicians who establish collaborative relationships with patients can enhance clinic attendance and adherence to therapy plans [36]. In a systematic review of longitudinal studies designed to reduce attrition in adults [37], a greater number of strategies was inversely related to attrition; however, of the 88 studies in this review, only 4 were randomized controlled trials (RCTs), underscoring the need for experimental research to test multiple strategies for reducing attrition. Telephone and electronic reminder systems that provided detailed information beyond basic appointment details, including resource sharing and rapport building, are effective in reducing attrition [38–41]. In adult obesity interventions, multi-component approaches, financial incentives, and self-monitoring decreased attrition [42]. Notably, none of the trials in this review were developed a priori to reduce attrition; they also neglected to include stakeholders as intervention co-designers, highlighting the need for well-designed trials that include families, clinicians, and researchers as partners.

People living with a chronic illness like obesity often have difficulty navigating the complex, fragmented healthcare system [43]. Such experiences catalyzed research on the impact of support workers known as patient or family navigators. Navigators have diverse backgrounds but similar roles—to help patients and families coordinate care [44], access community services [31], attend clinical appointments [45], overcome communication and information barriers [46], and receive social support and education [47]. These activities can transform healthcare delivery by improving access, satisfaction, and outcomes [43, 48, 49]. Family Navigation (FN) is a multifaceted care model delivered by navigators who explore barriers to accessing clinical care and help patients and families by facilitating self-management and access to care. Rather than providing clinical care, FN addresses barriers and provides social support [43]. Navigators advocate for, educate, and assist families with tailored support and access to resources within and beyond the healthcare system [43]. In adults, navigation improves clinic appointment attendance [50], treatment outcomes [43], and satisfaction with care [51], especially when patients and families require services across settings and sectors [52]. FN is a direct response to recommendations [53] for tailored support to families in pediatric obesity management. FN is novel in pediatrics [54], and evaluations are rare, underscoring the need for robust evidence on the effectiveness of this intervention [55].

Our goal is to conduct a feasibility study to prepare our team for a definitive RCT in which we will test the effectiveness of FN to reduce attrition in 6–17-year-olds in pediatric obesity management. To help our team prepare for this future RCT, the objectives of our randomized feasibility study are to (i) explore children’s and caregivers’ acceptability of FN and (ii) examine attrition, measures of study rigor and conduct, and responses to FN + Usual Care vs Usual Care using clinical, health services, and health economic data.

## Methods

### Study design

Our 2.5-year, multi-method, multi-center randomized feasibility study has two arms and parallel assignment. Our protocol follows the Consolidated Standards of Reporting Trials (CONSORT) extension for randomized pilot and feasibility trials [56] and the Standard Protocol Items: Recommendations for Interventional Trials (SPIRIT). Please see Table 1 for our SPIRIT checklist [57].

**Table 1 Tab1:**
[figure not shown]
Schedule of enrollment, interventions, and data collection

### Study setting

Our study will be conducted at two clinical sites in Canada (Alberta Children’s Hospital in Calgary, AB; Trillium Health Partners in Mississauga, ON). Children will be assigned to an experimental (FN + Usual Care) or control (Usual Care) group after they enroll in publicly funded, multidisciplinary, pediatric obesity management clinics at our two sites.

### Stakeholder collaboration

Stakeholders have participated in several areas of our research. First, our application for research funding included both one caregiver and one colleague who works as a “community connector”; they played key roles in designing our study and conceptualizing our FN intervention. Second, our Stakeholder Steering Committee (SSC) is co-chaired by a (i) caregiver with experience in providing lived experience to academic teams through research studies and developing clinical practice guidelines and (ii) academic researcher with expertise in health, stress, and coping as well as navigation and peer-to-peer support for families of children with complex care needs. The SSC also includes other caregivers, older children, health care managers, clinicians, and research team members, who will meet regularly (e.g., monthly by videoconference; ad hoc by email) throughout our study.

As recommended [58], our SSC will work in partnership through several iterative stages, including the following tasks and outcomes: (i) engage in sharing experiences, perceptions, and preferences on access and attrition in managing pediatric obesity; (ii) discuss and evaluate existing navigation models with relevance to pediatric obesity; (iii) review FN design, theory, and implementation components, including logistical and relational strategies to increase access and reduce attrition; (iv) review and select outcome measures and data collection tools; (v) participate in qualitative and quantitative data interpretation to inform FN refinements and contextualize findings relevant to children, families, and clinicians; and (vi) contribute to knowledge translation products. Non-academic SCC members will receive $25 (CAN) gift cards for participating in each meeting. Finally, we consulted with several stakeholders who work with children and families, including social workers, school support workers, to ensure our FN intervention addressed the perceived needs of families who often access services to support child and caregiver health and well-being.

### Sample size

We will recruit 108 participants (54 per group and per site). Feasibility studies do not include formal sample size calculations [56], but experts recommend 12–36 per arm [59, 60]. We will enroll 27 participants per arm per site. This sample will give a 95% CI of width ≤ 0.34 for the difference in group proportions, assuming attrition is ≤ 0.4 in the control group. A sample size of 54 per arm will also allow 95% CIs of width ≤ 0.29 for other outcomes (e.g., proportion recruited). The sample size calculation for our future definitive RCT will be based on data from this feasibility study.

### Participant inclusion and exclusion criteria

At clinic enrolment, eligible participants must (i) be 6–17 years old, (ii) have a BMI ≥ 97th percentile [61], and (iii) have a primary caregiver (parent/guardian) agree to participate. Children of any sex or gender are eligible. Participants will be excluded if caregivers cannot communicate in English (< 5% of families in our clinics) since FN will be available in English only.

### Recruitment and enrollment

Research staff will work with clinical teams to offer families details about our study at clinic enrollment. Clinical team members will ask families if they are interested in learning about research at our clinics (i.e., consent to contact). If families respond “yes,” a research coordinator (RC) will contact caregivers to provide additional details about our study to enable enrollment. This process mirrors our approach in past multi-center studies at our two sites, including the Canadian Pediatric Weight management Registry (CANPWR; [62]). As an observational study, CANPWR offered no direct benefit to families, yet we recruited 66% (*n* = 1320/1992) of all children approached. We expect families to have a greater interest in this study because they have the potential to benefit directly from study participation via FN. Our annual volume of new referrals (Calgary: *n* ~ 300; Mississauga: *n* ~ 240) makes our study highly feasible. Recruitment will span ~ 12 months.

### Randomization and blinding

Our team biostatistician will computer-generate a permuted-block randomization sequence using child age on the day of consent (6–9 years, 10–13 years, 14–17 years) and clinic (Edmonton, Calgary, Mississauga) as subgroups to achieve balance across ages and clinics. The randomization sequence will be uploaded to Research Electronic Data Capture (REDCap) for centralized online randomization. Research coordinators (RCs) will then enter participant details into REDCap and manage randomization at each site.

We will conduct our study to reduce the risk of errors, follow best practices for real-world trials [63], and apply pediatric-specific recommendations to minimize the risk of bias [64]. To minimize selection bias, our online allocation process will be managed by team members not delivering interventions. RCs will collect study data to minimize response bias. Data analyses will be led by team members with no family contact. Our team biostatistician will create the randomization sequence but be blind to group assignment to minimize detection bias. RCs, navigators, clinicians, and families will know group assignment. Virtual appointments, which will remain the most common appointment type throughout our study, will limit interactions between families, minimizing ascertainment bias.

### Trial interventions

Our experimental group will receive FN + Usual Care. FN will be co-designed by our SSC and aims to reduce attrition by managing barriers and eliminating constraints that limit access to care. FN will increase access to a moderate to high intervention dose, increasing success in managing pediatric obesity. Although the initial design has started, refinements to the FN intervention (e.g., enhance navigator training/support) will continue to be made with our SSC, informed by study data and experience. Our control group will receive Usual Care only.

### Family navigation

The FN intervention will be co-designed with our SSC, including both theoretical and practical elements. Through co-design, we will maximize child- and family-centeredness, pragmatism, and intervention relevance by co-creating health services *with* and *for* children, caregivers, and clinicians [65].

Our participatory approach draws on key elements of Experience-Based Co-Design (EBCD) [66], an orientation that focuses on understanding SSC members’ experiences with health services, identifying potential improvements, and making changes together. With co-design, we increase intervention relevance and appropriateness, bringing together people who possess experiential knowledge (children, caregivers) with people who have expert knowledge (clinicians, researchers); the two knowledge systems enrich each other. Our team members have substantial experience in co-designing and refining health services and interventions in partnership with stakeholders [67–71].

Our two clinics will have a navigator to deliver FN. Navigators will be trained and equipped with resources for individualized support to benefit families in managing pediatric obesity. Navigators will start by orienting families to the intervention and completing a detailed needs assessment, highlighting areas for support to manage barriers and remove constraints to accessing pediatric obesity management. Strategies used by the navigator may include (i) communicating via text message to schedule appointments, providing appointment reminders, celebrating successes, exploring solutions for barriers to care, and sharing educational resources; (ii) having flexible navigator appointments (evenings, weekends, virtual); and (iii) providing parking/transit passes in-person visits of families with navigators, clinicians, and researchers.

Navigator appointments will supplement family appointments with clinicians for pediatric obesity management, increasing professional contact. Navigators will use principles of motivational interviewing (MI) [72] and focus on listening to and validating family challenges, exploring the desire to continue pediatric obesity management. They will foster a safe, non-judgmental space for families to discuss expectations and experiences as well as empower families to access resources and services that optimize care within and beyond the clinic. Navigators will be flexible and responsive. In some cases, they will work intensively with families, liaising regularly with clinicians to integrate care. In other cases, they will interact with families exclusively. Family preferences and needs drive appointment frequency with navigators: weekly, biweekly, or monthly; virtual (videoconference or phone) or in-person, pandemic permitting; 30–60 min long. As a tailored intervention, FN acknowledges that the desire to maximize adherence to pediatric obesity management varies by family and that ambivalence is common in managing obesity [30]. Navigator–family discussions may include children and caregivers together or separately, based on preferences and needs. Navigators will work with the research and clinical teams to adhere to a communication and documentation protocol if families disclose information (e.g., child safety) beyond their scope of practice. Navigators will hold an undergraduate degree in a relevant field (e.g., psychology, nursing, social work), complete advanced training in MI, and receive ongoing mentorship to maintain proficiency [73]. Registered psychologist team members ([name]) will oversee training and mentorship with a model that maximizes MI skill development and fidelity. Each navigator will complete ~ 80 h of MI training (e.g., readings, workshop) as recommended to maintain competence [74]. At the study start, all navigators will participate in a virtual workshop on strategies to mitigate obesity bias and stigma [75, 76], which will be led by a team member with expertise in this area (AA). In readings and discussions, navigators will gain perspective and expertise on children and families from diverse backgrounds and cultures. During the study, psychologist team members ([name]) will use the MI Supervision & Training Scale [77] to provide structured feedback to navigators on proficiency, maximizing fidelity to MI within and between navigators. After giving detailed feedback to navigators on their first several sessions with families, our team members will review randomly selected sessions throughout the study to highlight areas of strength and improvement for navigators. Navigators’ MI sessions with families will be recorded digitally and uploaded to a secure platform for data storage.

### Usual care

Our control intervention is Usual Care for managing pediatric obesity, delivered similarly across our two clinics by multidisciplinary teams who follow family-centered care principles [78] and guidelines [79]. At clinic presentation, children will complete a comprehensive health assessment to inform lifestyle (e.g., diet, physical activity, sedentary activity, sleep) and behavioral goal setting and subspecialty medical referrals, if indicated. Children and caregivers attend clinic visits regularly to make and maintain healthy changes. Appointments with physicians occur at least every 6 months, and more frequently with other clinicians (e.g., dietitian, psychologist). The dose and duration of pediatric obesity management vary according to family needs, motivation, and illness severity. Our two clinics offer 1-on-1 virtual care by videoconference or phone, with in-person visits restarting, pandemic permitting.

### Duration of treatment and follow-up

Intervention duration is 12 months for both experimental (FN + Usual Care) and control (Usual Care only) groups. Qualitative data will be collected at 3 intervals (0 [baseline], 3–6, and 12 months post-baseline). Quantitative data will be collected at 4 intervals (0 [baseline], 3, 6, and 12 months post-baseline).

### Data collection and management

To assess children’s and caregivers’ perceived acceptability of FN (objective 1), we will complete ~ 30-min, semi-structured, 1-on-1 interviews with families (see Additional file 1 for caregiver interview guide). We will group children into 6–9 years, 10–13 years, and 14–17 years. These groupings are based on potential developmental differences that could influence participants’ perceptions and experiences of the intervention. For the 6–9 years group, only caregivers will be interviewed as children of this age may have difficulty giving detailed insights on accessibility, and caregivers are responsible for virtually all decision-making for children in this age range. For 10–13 years and 14–17 years groups, children and caregivers will be interviewed independently, although child-caregiver (dyad) interviews will be offered (i.e., interviews will be completed as a family if children feel more comfortable with their caregiver present). We plan to interview participants in the experimental group (*n* = 54 caregivers; *n* = 36 10–17-year-olds) three times: before FN intervention delivery (0 month [baseline]), mid-intervention (3–6 months post-baseline), and at intervention completion (12 months post-baseline). However, the final sample size may be lower if (i) data saturation is achieved along the way and/or (ii) families discontinue care prematurely or terminate study participation. RCs at our two sites will conduct interviews virtually (videoconference, phone) or in-person, pandemic permitting. Interviews will be audio-recorded, transcribed verbatim, and managed with NVivo 11 (QSR, Australia).

To evaluate attrition and measures of study rigor and conduct (objective 2), we will compare outcomes against pre-set success indicators. We have a conceptual definition of attrition (permanently discontinue care [19]), but a universal, operational definition does not exist [16, 17]. For this reason, our operational definition will include three categories: “yes,” “no,” and “unknown,” which will be recorded identically for experimental (FN + Usual Care) and control (Usual Care only) groups. If a child discontinues pediatric obesity management at any point up to 12 months post-baseline or if an appointment is missed or cancelled without rescheduling and we have no follow-up communication with the family after four phone/text messages over 4 weeks and no scheduled upcoming appointments, they will be categorized as “yes.” If a child remains active in pediatric obesity management at 12 months post-baseline, they will be classified as “no.” If their status cannot be confirmed, they will be classified as “unknown.” The exact date of attrition will be pinpointed as a child’s last recorded interaction with a pediatric obesity management clinician or navigator, confirmed via primary (child’s medical record, clinic scheduling system) and secondary sources (families, clinicians, navigators [experimental group only]).

In addition, we will measure several secondary outcomes given their established or possible links to attrition [80–85], which will be collected for descriptive purposes and hypothesis generation. RCs will review children’s medical records to retrieve sociodemographic and clinical data, using standard case report forms and processes that adhere to recommendations for medical record reviews to optimize accuracy [86, 87]. For child- and caregiver-reported data, families will complete gender-neutral surveys created using REDCap that will be accessible virtually by desktop, tablet, or smart phone.

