2.What proportion of participants approached were eligible?			≥ 90% approached were eligible		
3.Did recruited participants complete consent/assent procedures?			≥ 95% recruited participants completed consent/assent procedures		
4.Did recruitment lead to successful enrollment?			100% sample size goal achieved		
5.Did participants agree to randomization?			≥ 95% participants agreed to be randomized		
6.Did randomization yield equality across groups?			Equal numbers of participants randomized to experimental and control groups		
7.Were blinding procedures effective?			100% analysts remained blinded to group assignment		
8.Were outcome assessments completed?			≥ 95% participants retained in the study completed outcome assessments		
9.How complete were outcome assessments at all study measurement intervals?			≥ 95% outcome assessments were complete		
10. Were outcome assessments burdensome for families?			≥ 90% children and caregivers disagreed that outcome assessments were burdensome		
11. Was study protocol acceptable to children and caregivers?			≥ 90% children and caregivers agreed study protocol was acceptable		
12. Was the level of attrition adequate within experimental (Family Navigation + Usual Care) and control (Usual Care only) groups at 12 months?			Experimental (FN + UC): 15–25% attrition Control (UC): 30–40% attrition		
13. Was collection of attrition data adequate to calculate sample size for definitive RCT?			≥ 95% participants had attrition data collected by 12 months post-baseline		
14. Were logistics of running a multi-center trial assessed?			Review procedures (ongoing and end-of-grant) with investigators, research staff, navigators		
15. Did all components of the protocol work together adequately?			Review procedures (ongoing and end-of-grant) with investigators, research staff, navigators		

^a^Comments and Feasibility Data columns will be populated with study data collected during our study; example provided for context

^b^Criteria column thresholds based on objective criteria (when possible) and experience gained through study implementation as well as data analysis and interpretation with Stakeholder Committee and research team

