For objective 2 (measuring attrition; study rigor and conduct; clinical, health services, economic outcomes), we will describe continuous data by summaries (means, medians, ranges) and categorical variables with frequency distributions. Data will be described for each group (e.g., sex, gender), stratification (e.g., age [6–9 years, 10–13 years, 14–17 years]), and clinic (Calgary, Mississauga). Group differences in outcomes will be calculated with 95% CIs. To complete power calculations for our definitive RCT, the 95% CI for the primary outcome (attrition yes/no at 12 months post-baseline) will be used. *R* [99] will be used for statistical analysis by a data analyst blinded to group assignments. Our SSC will discuss and contextualize study findings. REDCap will house quantitative data and generate data files for analyses. Consistent with feasibility studies [56], our analyses will be descriptive. Uncertainty exists on what elements(s) of FN are essential to optimize intervention effects [43]. In response, the participatory nature of our research, inclusion of qualitative and quantitative data sources, and heavy participation of our SSC will provide a full assessment of FN, revealing vital insights into how our experimental intervention can optimize treatment impact for managing pediatric obesity in our future definitive RCT.

Qualitative data analysis will occur throughout the study. Quantitative data analysis will occur at study completion only. Based on literature reviews of attrition and pediatric obesity management [16, 17], subgroup analyses will be exploratory and descriptive. We will describe attrition and other outcomes (e.g., HRQoL, intervention dose received) in experimental and control groups to explore potential differences by age, sex, gender, clinic, and changes within and between these subgroups over time.

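### The attrition categories overlap for children who lapse and return, make no exception for an agreed end of care, and are not mapped to the yes/no primary outcome

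*Protocol article*

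**What the plan says.** **Concept.** Data collection and management states: "We have a conceptual definition of attrition (permanently discontinue care [19"). The Abstract adds prematurity: "some families discontinue care prematurely (i.e., attrition").

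**Operational rule (same section).** There are three levels.
- *Yes*, first limb: "If a child discontinues pediatric obesity management at any point up to 12 months post-baseline".
- *Yes*, second limb: a missed or cancelled visit that is not rebooked, with "no follow-up communication with the family after four phone/text messages over 4 weeks and no scheduled upcoming appointments".
- *No*: "If a child remains active in pediatric obesity management at 12 months post-baseline".
- *Unknown*: status cannot be confirmed.

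The date of attrition is the last recorded contact with a clinician or navigator.

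**Length of care.** Usual care says: "The dose and duration of pediatric obesity management vary according to family needs, motivation, and illness severity". Duration of treatment and follow-up sets the intervention at 12 months in both arms.

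**Use.** Data analyses takes the confidence interval for "the primary outcome (attrition yes/no at 12 months post-baseline) will be used" in powering the definitive trial. Table 2, criterion 12, sets attrition bands of 15–25% (navigation arm) and 30–40% (control). Criterion 13 asks that at least 95% of "participants had attrition data collected by 12 months post-baseline".

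**The concern.** The categories should be mutually exclusive, should follow the stated concept and should lead to the outcome that is analysed. As written they fall short on each count.

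- **Overlap.** Neither *yes* limb requires that the child stay away. A child can meet one early, return, and also meet the *no* rule. No order of precedence and no re-engagement rule is given.
- **No planned-end exception.** The first limb does not ask why care ended, yet the concept is premature discontinuation and the length of care is said to vary.
- **Three levels, two outcomes.** *Unknown* is not assigned to either side of the yes/no outcome. Criterion 13 does not say whether an *unknown* counts as data collected.

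This is the outcome that the article calls primary. It decides criterion 12 and feeds the size of the definitive trial. Navigation is meant to keep families in care, so families who lapse and return are cases that matter to the comparison. Research coordinators collect the study data and know the allocation (Randomization and blinding). Cases that the rule leaves open would have to be settled by judgment that is not blinded.

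**Working it through.** **1. The plan's own figure.** Sample size gives a 95% CI width of at most 0.34 for the difference, with 54 per arm and control attrition up to 0.40. Assuming 0.20 in the navigation arm (mid-band in criterion 12; the article does not state it):

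width = 2 × 1.96 × √(0.40×0.60/54 + 0.20×0.80/54) = 0.337.

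This agrees with the plan and is not in dispute.

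**2. Three children put through the rule as written.**

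| Child | *Yes* rule | *No* rule | Stated concept |
|---|---|---|---|
| Silent by month 4 (contact attempts exhausted, nothing booked), active at month 12 | met | met | not permanent, so not attrition |
| Care ended by agreement at month 9 | met (first limb) | not met | not premature, so not attrition |
| Status cannot be confirmed | not met | not met | *unknown*; no place in yes/no |

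The first row has a single answer only if the *no* rule is read as requiring uninterrupted care, which the text does not say. That reading would score a temporary lapse as permanent discontinuation.

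**3. How much one child weighs.** 1/54 = 1.9 points. A 10-point band spans 0.10 × 54 = 5.4 children, so from mid-band about 2.7 children reach the edge.

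**4. Sensitivity to lapsed-and-returned children or agreed endings.** Assumed base: 11/54 (20.4%) navigation versus 19/54 (35.2%) control, both near mid-band. Future n per arm uses the pooled-variance formula, two-sided 5%, 80% power:

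n = [1.96√(2p̄(1−p̄)) + 0.842√(p₁(1−p₁)+p₂(1−p₂))]² / (p₁−p₂)².

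| Children moved from *yes* to *no* | Navigation | Control | Difference (points) | n per arm |
|---|---|---|---|---|
| none | 20.4% | 35.2% | 14.8 | 143 |
| 3 in each arm | 14.8% | 29.6% | 14.8 | 123 |
| 3 in navigation only | 14.8% | 35.2% | 20.4 | 70 |
| 3 in control only | 20.4% | 29.6% | 9.3 | 343 |

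In every altered row at least one arm falls just below its criterion 12 band (15% or 30%).

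**5. Sensitivity to *unknown*.** If *unknown* means not collected, criterion 13 allows 0.05 × 108 = 5.4, so 5 children. Keeping 11 and 19 confirmed *yes*, with the unknowns among the remaining children:

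| Unknowns (navigation/control) | Handling | Navigation | Control | Difference (points) | n per arm |
|---|---|---|---|---|---|
| 2/3 | counted *no* | 20.4% | 35.2% | 14.8 | 143 |
| 2/3 | excluded | 11/52 = 21.2% | 19/51 = 37.3% | 16.1 | 125 |
| 2/3 | counted *yes* | 13/54 = 24.1% | 22/54 = 40.7% | 16.7 | 123 |
| 3/2 | counted *yes* | 14/54 = 25.9% | 21/54 = 38.9% | 13.0 | 204 |

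The counts in steps 4 and 5 are illustrations. The article gives no frequency for any of these groups.

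**The case against.** **The whole text points to one answer for a child who returns.** The concept is permanent discontinuation, the outcome is stated at month 12, and the attrition date is the last recorded contact, which for a returning family falls near month 12. Quantitative analysis happens only at study end, so nothing fixes an early *yes*. This shows the likely intention. It does not remove the limb that says otherwise.

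**Planned completion is never mentioned.** This stands as a limit. A reader might infer that the trial counts planned completion, or leaving a pediatric clinic at 18, as attrition. The article says neither and gives no discharge age, and the 12-month intervention may make agreed endings uncommon. What remains is a literal rule without an exception.

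***Unknown* may be handled in an analysis plan that is not shown.** This is fair. A reader might infer that unknowns are dropped and that this biases the rates downward, more so in control. The article does not say they are dropped. The typical loss (missed visit, no reply, nothing booked) is already *yes*, and status is recorded in the same way in both arms, with medical records and the scheduling system as primary sources. If five leavers, all in control, were dropped, 14.8 points would become 14/49 − 11/54 = 8.2. That is an extreme allocation: with a 2/3 split it is 16/51 − 9/52 = 14.1. What stands is that the two stated forms of the outcome do not map onto each other.

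**Timing.** A reader might infer that families who fall silent in the last month cannot be classified by month 12. Dating attrition to the last contact and analysing at study end largely answer this. A sentence letting the 4-week contact period finish is enough.

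**The study is a descriptive feasibility study**, and the article acknowledges that no universal operational definition exists. That limits the consequences, but the same data are meant to size the definitive trial.

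**Conclusion.** The point holds as a defect in the stated rule. The categories are not mutually exclusive for children who re-engage, they are tied to neither permanence nor prematurity, and they do not map to the yes/no primary outcome. Read literally, the rule can give a wrong primary outcome for an individual child.

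The document does not support the stronger conclusion that the attrition rates will measure something other than intended, or will be biased in a known direction. Without frequencies, neither size nor direction can be computed. What can be shown is sensitivity: 1.9 points per child against 10-point bands, and a future sample size moving from 143 to between 70 and 343 per arm when three children change category. These figures rest on the assumed 11/54 and 19/54, the assumed reclassifications, a two-sided 5% level and 80% power.

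**What to change.** 1. Classify status once, as of month 12, allowing the 4-week contact period to run out for visits missed in the last month.
2. State precedence: a child in active obesity-management care at month 12 is *no*, even after an earlier lapse. Report lapses separately.
3. Record the reason for ending care, and report agreed completion or transfer separately from attrition.
4. Prespecify one mapping of *unknown* to the yes/no outcome, and report best-case and worst-case bounds by arm. Say whether *unknown* counts as collected under criterion 13. Counting *unknown* as attrition is one option, but it should not be called conservative: if unknowns cluster in control, it enlarges the apparent benefit of navigation compared with excluding them.

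The cost is definition wording, one reason code on the case report form and a record check up to 4 weeks later. Quantitative analysis is planned only at study completion, so the rule can be settled before any outcome comparison.
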